#### Secondary outcome measures

General psychological distressICD-10 symptom rating German version (ISR [63])Patient Health Questionnaire German version (PHQ 9 [64])

For the evaluation of intra- & intersession processes intra-session processes will be assessed using the Patient Session-Assessment Questionnaire German version (STU-P, ger. orig.: “Stunden Beurteilungsbogen für Patienten”; [65]) and intersession processes will be assessed using the Intersession-Questionnaire German version (ISF, ger. orig.: “Intersession Fragebogen”; [66]).

### Data collection

All self-report measures will be collected by computerized questionnaires, using different online survey platforms. For T0, T1 & T2 evaluation (see Fig 2), Google forms will be used. For evaluating intra- and intersession processes forms included at our study websites will be used. Table 2 shows an overview of all measurement instruments used across the different measurement time points of the study. Access to any data is restricted to trial personnel and investigators. Name, e-mail address and telephone number are required for organizational purposes and for sending the links for the online data collection. These data are recorded independently of the other study-related data only by the study director in an Excel spreadsheet and kept in a password-protected laptop. Nobody else has access to it. All other data will be collected pseudonymously via a subject code to be generated by the patients themselves (= individual code). Anonymity is to be protected on different levels. At the level of the practitioner, it is protected by the professional laws. The practitioners are bound to secrecy according to the Austrian Psychologists’ Act and the German Psychotherapists’ Act. Accordingly, no information about the persons and their treatment may be disclosed to the outside. Only during supervision and intervision may the contents of the units be discussed anonymously. However, the supervisors are also subject to the same professional laws as the therapists, so that the data of the subjects are also protected at this level. At the level of research data, the pseudonymization by means of individual codes makes it impossible to assign the data to any specific person, unless the person discloses his or her individual code. At the level of the actual personal data, anonymity is ensured by the fact that only the study director has access to this data and only is aware of it. However, even he or she cannot establish an assignment of the names to the data because he or she does not have the individual codes. The personal data are accessible only through a password-protected table in an equally protected laptop.

**Fig 2 pone.0299803.g002:**
[figure not shown]
SPIRIT schedule of enrollment.

**Table 2 pone.0299803.t002:** Diagnostic materials.

Assessments	Study period						
	Prescreening	Screening	PRE evaluation (T0) Before session	Intervention (10 weeks) After session		POST evaluation (T1)	FOLLOW-UP evaluation (T2, after 3 months)
				Before session	After session		
BAI	×		×			×	×
PAS	×		×			×	×
GAD-7	×		×			×	×
FQ	×		×			×	×
PPTI			×			×	×
FS			×			×	×
SWLS			×			×	×
ISR			×			×	×
PHQ-9			×			×	×
STU-P					×		×
ISF				×			
MINI-DIPS		×					
PSS-K		×					
Informed consent		×					
Third-party evaluation by therapists		After screening	Before therapy			After therapy	

BAI: Beck Anxiety Inventar, PAS: Panic and Agoraphobia Scale, GAD-7: Generalized Anxiety Diagnostic, FQ: Fear Questionnaire, PPTI: Positive Psychotherapy Inventory, FS: Flourishing Scale, SWLS: Satisfaction with Life Scale, ISR: ICD-10 Symptom Rating, PHQ-9: Patient Health Questionnaire, STU-P Patient Session-Assessment Questionnaire (ger. orig.: “Stunden Beurteilungsbogen für Patienten”), ISF: Intersession-Questionnaire (ger. orig.: “Intersession Fragebogen”), MINI-DIPS: Diagnostic short interview for mental disorders (ger. orig.: “Diagnostisches Kurzinterview bei psychischen Störungen”), PSS-K: Personality Disorder Screening—Short Form (ger. orig.: “Persönlichkeitsstörung-Screening—Kurzform”)

### Statistical analysis

The primary outcome is pre-post and follow-up change in anxiety and positive outcomes (overall life satisfaction, happiness experience). In this study, we will conduct an intention-to-treat analysis. For the statistical analysis of the primary outcome, we will conduct a repeated measures ANOVA with three independent variables (PPT, CBT, CG). For the process study, two ANOVAs will be conducted with two independent variables each (emotional experience positive/negative and level of session activity high/low).

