## Methods

### Design and setting

The planned study is a randomized-controlled comparative study and will be realized as a ten-week online group therapy with the following three treatment conditions to which participants will be randomly assigned: Group 1: An intervention condition in which participants receive PPT treatment, Group 2: an intervention condition in which they receive CBT treatment, and Group 3: a control condition designed as PPT treatment with minimal therapeutic supervision. Participants in the control condition receive the same material, content, and exercises as the participants in PPT treatment condition. However, they only have three online video call meetings and work through the content on their own during the remaining weeks. There are three measurement time points for testing the efficacy hypotheses: An online questionnaire survey before treatment begins (PRE measure), a second identical survey after treatment will be completed (POST measure), and a third identical survey three months after treatment will be ended (FOLLOW-UP measure). This results in a 3×3 between- and within-subjects design. The hypotheses regarding the intra- and intersession processes will be tested by means of weekly surveys in each case before the therapy sessions (intersession processes) as well as after the therapy sessions (intrasession processes). Fig 1 shows the study design and the different steps of the procedure in a chronic flow diagram. The study is conducted at the Department of Clinical Psychology and Psychotherapy at the University of Salzburg. Prior to initiation, the study design was submitted to and approved by the Ethics Committee of the University of Salzburg (EK-GZ: 22/2021). The study is registered at the German Clinical Trial Register (№ DRKS00027521; date of registration February, 3^rd^ 2022; type of registration: prospective). The full details according to the World Health Organization Trial Registration Data Set standards are shown in Table 1. For a complete description of the relevant information and their position in the manuscript according to the SPIRIT checklist, please refer to S1 Checklist.

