### Sample size

The sample size was calculated using a power analysis (G*Power 3.1; [53]), given an alpha error of.05 and a power ≥.80, resulting in a sample size of *N* = 165. Accordingly, 55 persons would be included in each of the three intervention groups. Effect size estimates resulted from findings of previous studies [12, 19]. Since a high dropout rate is to be expected, a significantly higher number of subjects will be screened and admitted to the study.

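### The repeated measures ANOVA named for the primary outcome does not, as conventionally run, deliver the promised intention-to-treat analysis once T1 or T2 scores are missing

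*Protocol article*

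**What the plan says.** Under Statistical analysis, the protocol article sets the analysis population: "In this study, we will conduct an intention-to-treat analysis". The next sentence sets the model for the primary outcome: "we will conduct a repeated measures ANOVA with three independent variables (PPT, CBT, CG". The outcome covers both later time points: "The primary outcome is pre-post and follow-up change in anxiety and positive outcomes". Design and setting describes the layout: "This results in a 3×3 between- and within-subjects design".

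Under Sample size, the article expects substantial loss and gives its only response: "Since a high dropout rate is to be expected, a significantly higher number of subjects will be screened and admitted to the study". No dropout rate is given, overall or by arm. The target of 165 is described as "Accordingly, 55 persons would be included in each of the three intervention groups".

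Under Randomization and blinding, allocation follows completion of the T0 questionnaire. The article does not say how a participant with a missing T1 or T2 score stays in the analysis.

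**The concern.** A conventional repeated measures ANOVA needs a score on every occasion. With T0, T1 and T2 in one model, a participant who answers at T1 but not at T2 is deleted from the whole analysis, so the observed T1 score is lost to the T1 comparison too. An intention-to-treat analysis is meant to keep everyone randomised, in the arm assigned. Two adjacent sentences therefore promise one population and name a method that normally analyses another.

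What is at stake is comparability. If control participants who are doing poorly leave more often, the remaining control participants look better and the PPT and CBT advantages over control shrink. The opposite pattern inflates them. The arms differ in therapist contact (three meetings in the control arm, weekly sessions over ten weeks in the others), so unequal dropout is plausible, though the article does not establish it. Admitting more people yields a larger group of completers selected in the same way.

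**Working it through.** **1. The plan's own figure.** The Sample size section gives "given an alpha error of.05 and a power ≥.80, resulting in a sample size of" 165, and on the effect size only "Effect size estimates resulted from findings of previous studies [12, 19". Effect size, test family and correlation between measures are not stated, so 165 cannot be reproduced from the article alone. One set of assumptions does reach it: the between-groups test of a repeated measures ANOVA with 3 groups, 3 measures, f = 0.20 and correlation ρ = 0.5.

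- Noncentrality λ = N·f²·m / [1 + (m − 1)ρ] = 165 × 0.04 × 3 / 2 = 9.9
- Power at α = .05 with 2 and 162 degrees of freedom: 0.804

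**2. What deletion does to numbers.** These rates are assumed. Completers = 165(1 − d); the number to randomise to keep 165 completers = 165/(1 − d), rounded up.

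| Assumed share missing T1 or T2 | Completers if 165 are randomised | Power under step 1 | Randomised to keep 165 completers |
|---|---|---|---|
| 10% | about 148 | 0.76 | 184 |
| 20% | 132 | 0.70 | 207 |
| 30% | about 116 | 0.64 | 236 |
| 40% | 99 | 0.57 | 275 |

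The last column is the route the article says it will take, without giving a number. If enough people are admitted, the power loss in the third column does not arise. Selection is unaffected by it.

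**3. What deletion can do to the estimate.** Assumptions: SD 1; T0–T1 correlation .6; true T1 difference .30 SD between PPT and control; 20% loss at T2 in PPT, at random; 34% loss at T2 in control, with the log-odds of loss rising by .4 per SD of worse T1 score.

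- Raw T1 difference among completers: about .17, a shift of .30 − .17 = .13 SD.
- The outcome is change, and the control completers' T0 mean shifts too, by .6 × .13 ≈ .08.
- Shift in the change contrast: .13 − .08 ≈ .05.
- Estimated difference in change among completers: .30 − .05 ≈ **.25 SD**.

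An analysis of all observed T1 scores returns .30 here, but only because the scenario has no loss at T1.

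**4. Other assumed scenarios.** No true difference between arms; correlations .5 (T0–T1 and T0–T2) and .7 (T1–T2); loss depends on the T1 score in both arms, with log-odds slope 0.5 to 1 per SD.

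- Dropout 20% vs 40%, or 10% vs 30%: completers show a spurious between-arm difference of about .05 to .08 SD in T1 change and .02 to .03 SD in T2 change. Using all observed T0 and T1 scores leaves an error of at most .005 SD in T2 change.
- Equal dropout of 20% or 30% with the same mechanism: between-arm bias is about zero, while within-arm improvement at T2 is overstated by about .02 to .05 SD.

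**The case against.** The strongest reply is that the article never mentions listwise deletion or a completer set. Intention-to-treat and an ANOVA are compatible if missing values are imputed first, or if the label loosely covers a mixed model, and missing-data handling is commonly left to a full protocol or analysis plan that is not shown. This stands in part: it rules out asserting as fact that the primary analysis is a completer analysis. It does not remove the point, because the article itself fixes the model, and that model as conventionally run conflicts with the sentence before it.

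A reader might also infer a loss of power. The documents do not support that: over-enrolment is there to offset dropout, and shrinking 165 to its completers describes a plan the article does not set out.

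A reader might take the .13 SD shift in raw T1 scores as the bias. The stated outcome is change, where the same scenario gives about .05 SD.

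Unequal dropout is assumed. Control participants also receive weekly emails, mail contact with therapists and couple teams, and ten 120-minute sessions may themselves cause dropout. Finally, T0 should not be missing for anyone randomised, since allocation follows it; the losses at issue are at T1 and T2.

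**Conclusion.** The mismatch holds in a limited form. As conventionally run, the named ANOVA deletes participants who lack T1 or T2, including their observed T1 scores, so it does not by itself deliver the intention-to-treat analysis promised one sentence earlier, in a trial that expects high dropout. Over-enrolment protects numbers, not comparability.

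The bias is a risk whose size the article does not allow one to calculate. Under the assumed control-arm loss in step 3, .30 SD in change becomes about .25 SD. Under the other unequal-dropout scenarios the between-arm error is about .02 to .08 SD, and with equal dropout of the same cause it is near zero. The conclusion that the text needs changing rests on the wording, not on these figures. This should be fixed; the evidence does not show that the trial's conclusions would be overturned.

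**What to change.** Replace the ANOVA as primary analysis with a likelihood-based mixed model for repeated measures that includes all randomised participants by assigned arm and uses T0 and every available T1 and T2 score, without listwise deletion. Alternatively, keep the ANOVA and pre-specify multiple imputation before it. Either would reconcile the two sentences. The mixed model relies on data being missing at random given the observed scores, so add one sensitivity analysis for data missing not at random, for example delta-adjusted multiple imputation with separate shifts for the control and treated arms.

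The cost is revised wording and code, with no new data; the downside is slightly more complex analysis and reporting.

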### Interventions

The first step in conducting the study was the development of the treatment manuals and therapy materials. Two treatment manuals were developed, one each for PPT and CBT treatment. The PPT manual is based on the official PPT manual by [10] and adapted for the study. Because of economic reasons instead of 15 sessions as in the original manual, only 10 therapy sessions are conducted in the present study. In addition, the individual PPT topics were adapted and exercises from the personal PPT application repertoire of the study leaders were incorporated. As in the original manual, a gratitude diary will be filled out daily by the participants accompanying the therapy. In the individual sessions, various positive-psychological interventions are carried out, e.g., participants learn how to handle and use positive emotions, work out their personal character strengths and learn how to use them in concrete anxiety situations. Other topics covered in the PPT treatment include gratitude, optimism, a positive self-image, self-compassion, resilience, everest goals, best-possible self, and future perspective. The CBT manual is conceptually adapted to the PPT treatment and also comprises 10 therapy sessions. The exercises and content were selected based on the German language therapy tools for anxiety disorders by [56]. In the CBT treatment, participants are required to practice the relaxation exercise Progressive Muscle Relaxation according to Jacobsen on a daily basis. In CBT treatment, participants learn how to deal with anxiety thoughts and behavior and how to restructure stressful anxiety related cognitions. For this purpose, various cognitive-behavioral therapy interventions are carried out, e.g., the development of an individual explanatory model, the worry chair and various attention and breathing exercises. An elementary part of the treatment is an exposure exercise, which is worked towards during therapy. Other topics covered in CBT treatment include the three levels of anxiety (body, thoughts, behavior), the vicious cycle of anxiety, and mindfulness. In addition to the treatment manuals, workbooks were created for the participants to work on during the therapy. The workbooks contain all organizational details, theoretical topics as well as all exercises and worksheets that must be done in the video-supported sessions or as homework. Additional websites (created by Webflow) were provided for both intervention groups to make additional therapy tools available, such as videos or questionnaires. That aside the websites are also used to conduct part of the data collection. The implementation of the treatments takes place online via videoconferencing using the Zoom platform. Participants in the two intervention conditions (PPT & CBT) will meet once a week with the treatment providers for a 120-minute online presence meeting, in which the content of the respective sessions will be conducted according to the manual. In addition, participants will be given homework assignments to complete independently for the week between the face-to-face sessions. These homework assignments will be discussed in the group at the beginning of each session. The control group is designed as a PPT with minimal therapeutic supervision. The participants will receive the same PPT workbook as the intervention group and accordingly will work on the same topics and exercises over the ten weeks as the participants in the PPT intervention group. The difference between the two groups lies in the therapeutic support. In the control group, a video-supported meeting with the therapist will be held only three times: In the first session, halfway through therapy in the fifth session, and in the last session. In between, participants receive an overview email at the beginning of the week and a reminder email at the end of the week. Apart from the possibility of mail contact with the therapists, the participants in the control group carry out the exercises independently with the help of the workbook and the materials on the website. For the control group, as for the intervention groups, a separate website is provided. Another important component of all treatment conditions is the formation of teams of two clients (couple teams) within each therapy group. These teams will be formed in the first session of therapy and will remain in place throughout the duration of therapy. Participants are encouraged to meet at least once a week to discuss the week’s exercises and topics with each other. In some cases, specific reflection questions will be provided in the individual exercises in the workbook. Depending on the possibilities of the participants, the meeting could take place online via a telephone call or video call or in person. When forming the couple teams, deliberate care was taken to divide the participants according to local proximity.

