### Trial governance

The Trial Management Group consists of the principal investigator, the study director ([name]) and is supported by two study assistants. The Management Group will provide overall management of the study including set-up of the study, recruitment, managing mails, and interpretation of results. In addition, eleven therapists (psychological psychotherapists in training) support the study by conducting the therapy groups. In preparation for the study, therapy manuals, websites and workbooks were developed for the different intervention groups by the principal investigator, the study director and a study assistant. Overall supervision of the trial is provided by the principal investigator. The therapists were trained in the manuals and for screenings by the project management. All therapists were trained in both manuals in order to be able to adopt both intervention groups (PPT and CBT) as needed during the course of the various study runs. At regular intervals, the therapy sessions are checked for their manual compliance and the therapists receive supervision by qualified psychotherapists and supervisors.

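### All three arms are delivered in therapy groups, but the named repeated measures ANOVA treats participants as independent; if outcomes correlate within groups, type I error exceeds the nominal .05

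*Protocol article*

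**What the plan says.** For the primary outcome the article names one model: "we will conduct a repeated measures ANOVA with three independent variables (PPT, CBT, CG" (Statistical analysis). No term for therapy group, couple team or therapist appears there, and no ICC or design effect appears anywhere in the article.

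Delivery is described in other sections:

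- Design and setting: the study "will be realized as a ten-week online group therapy with the following three treatment conditions".
- Interventions: a component of every condition is "the formation of teams of two clients (couple teams) within each therapy group". The pairs stay together throughout and are encouraged to meet weekly. The PPT and CBT arms have weekly 120-minute sessions; the control arm has three video meetings.
- Trial governance: "eleven therapists (psychological psychotherapists in training) support the study by conducting the therapy groups". All of them are trained in both manuals.
- Randomization and blinding: allocation is by individual participant, and the authors themselves run the control condition.

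The Sample size section plans N = 165, "given an alpha error of.05 and a power ≥.80": "Accordingly, 55 persons would be included in each of the three intervention groups". On the effect size it says only "Effect size estimates resulted from findings of previous studies". Its one reason for exceeding 165 is attrition: "Since a high dropout rate is to be expected, a significantly higher number of subjects will be screened and admitted to the study".

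**The concern.** A repeated measures ANOVA models the correlation between measurements on one person. It has nothing for correlation between people. Here people are treated together: they share sessions, discuss homework in the group and work in fixed pairs. Their T1 and T2 outcomes may therefore resemble each other more than those of people in different groups.

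Therapy groups are nested in arms, so any such correlation enters the between-arm comparison in full. One unusually good or bad group shifts its arm's mean, and the ANOVA reads that shift as if it came from independent people. At stake are the true error rate behind the stated alpha of .05, the width of the confidence intervals, and the planned power.

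**Working it through.** **Inputs from the article.** 3 arms, 55 per arm, 3 time points, alpha .05, power at least .80.

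**Inputs not in the article (assumed).** Group size m = 8, so 55/8, or about 7 groups per arm; ICC from 0 to .10; correlation of .5 between a person's time points; a group effect at T1 and T2 only, because T0 is measured before allocation.

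**Step 1: the planned N.** N = 165 cannot be reproduced from stated inputs, because effect size, test family and correlation over time are not given. One set of assumed inputs reaches it: repeated measures ANOVA, between factors, f = 0.20, ρ = .5. The noncentrality is f²·N·3/(1 + 2ρ) = 0.04 × 165 × 3/2 = 9.9, which on 2 and 162 degrees of freedom gives power .804. That calculation assumes independent participants. A one-way ANOVA with f = 0.25 gives 159 instead.

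**Step 2: design effect and type I error.** The design effect is DE = 1 + (m − 1) × ICC, and standard errors are understated by a factor √DE. Type I error is approximately P(χ²₂ > 5.99/DE) for three arms and 2·[1 − Φ(1.96/√DE)] for two arms. At ICC .05, DE = 1 + 7 × .05 = 1.35 and P(χ²₂ > 4.44) = .109.

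| ICC | DE | Effective n per arm (55/DE) | Type I error, three arms | Type I error, two arms |
|---|---|---|---|---|
| 0 | 1.00 | 55 | .050 | .050 |
| .01 | 1.07 | 51 | .061 | .058 |
| .02 | 1.14 | 48 | .072 | .066 |
| .05 | 1.35 | 41 | .109 | .092 |
| .10 | 1.70 | 32 | .172 | .133 |

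Simulating the group-by-time F test itself (4000 runs, groups of 8) gave .050 at ICC 0, .073 at .02, .112 at .05 and .172 at .10. At ICC .01 a run of 3000 gave .061.

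**Step 3: sensitivity to group size.** The three-arm formula at ICC .01, .05 and .10 gives .058, .091 and .136 for groups of 6, and .064, .127 and .207 for groups of 10.

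**Step 4: weaker clustering in the control arm.** With no clustering there, the simulated three-arm test (groups of 8) is .086 when PPT and CBT have ICC .05, and .124 when they have .10. With .02 in PPT and CBT and none in control it is .061. Allowing a little control-arm clustering gives .088 for .05 with .01. For .10 with .02, separate runs gave .128 and .148. The PPT-versus-CBT comparison does not involve the control arm, so the two-arm column stands for it.

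**Step 5: power.** Take the one-way effect size that gives about .80 power at N = 165, f = 0.2435 (noncentrality 165 × 0.0593 = 9.78). With ICC .05 and groups of 8, effective N is 165/1.35 = 122, noncentrality falls to 122 × 0.0593 = 7.2, and power to about .66. It is about .77 at ICC .01 and .55 at ICC .10.

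Couple teams are a second level of clustering. They are not included in these figures.

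**The case against.** The strongest reply is that the harm is conditional. A reader might infer that type I error is known to exceed 5% and that every between-arm p-value is wrong. The article does not support that: it gives neither group size nor ICC, the inflation is slight at ICC .01, and there is none at ICC 0. This stands, and the size can only be given as a range.

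The control arm meets three times and otherwise works alone, so equal clustering in all arms probably overstates the three-arm figures. This also stands; it reduces the inflation without removing it.

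A reader might infer that each group has one shared therapist whose effect adds to the problem. The Interventions section speaks of treatment providers in the plural. Because the therapists are trained in both manuals, a therapist effect could be partly common to PPT and CBT and partly cancel. Group and couple-team effects would not cancel in this way.

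A reader might also infer that N = 165 certainly contains no allowance for clustering. The match in Step 1 rests on assumed inputs; it suggests this but does not prove it.

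Last, a journal article is condensed, and an ANOVA can carry a nested random group factor. But the article does commit to a primary model and names arm as its only between-subject factor. That is a stated choice that does not fit the delivery, rather than a detail left to an analysis plan.

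**Conclusion.** The point holds in conditional form. The named primary model assumes independence between participants, and the group delivery in every arm gives good reason to doubt that. The direction of the error is clear: any positive within-group correlation makes the between-arm tests too liberal.

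Its size depends on assumed values. For groups of 8 it runs from negligible at ICC .01 to roughly double the nominal level at ICC .05 and more than triple at ICC .10, and is smaller for the three-arm test if the control arm clusters little. The planned power is optimistic under the same conditions.

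One limit cannot be modelled away. Because the authors run the control groups, therapist and arm are confounded there.

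**What to change.** - **Model.** Replace the repeated measures ANOVA by a linear mixed model for the three time points with a random effect for therapy group at T1 and T2. Let the group variance differ between the control arm and the PPT/CBT arms. Use Kenward-Roger or Satterthwaite degrees of freedom, since there may be only about 7 groups per arm. Report the ICC. Add couple team as a sensitivity analysis.
- **Therapist.** Examine a therapist effect only between PPT and CBT, and state the confounding in the control arm as a limitation.
- **Identifiers.** Record arm, therapy group and couple team with each pseudonymous questionnaire record at the time of collection. The Data collection section keeps names apart from self-generated codes and says that even the study director cannot connect them, so it offers no route for adding these fields later unless participants disclose their codes.
- **Sample size.** State that power of at least .80 at N = 165 holds only without clustering, and give an example with its assumptions, such as about .66 for groups of 8 and ICC .05.

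The cost is revised analysis wording and code and a few extra data fields. Confidence intervals will be wider if groups do cluster. The data record becomes slightly more identifying, most of all through the two-person team code, so its handling needs a stated procedure.
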